**Figure 3 BMJOPEN2016012795F3:**
[figure not shown]
Trial pathway for the usual care group. CXR, chest X-ray; USS, ultrasound scan; IPC, indwelling pleural catheter; QoL, quality of life.

From day 2 to 5 patients will be assessed for complications, drain output and lung re-expansion. If clinically possible, any steroids will be discontinued. Once full lung re-expansion is confirmed on X-ray (defined as full re-expansion of the lung to the chest wall or only blunting of the costophrenic angle on the affected side), talc slurry will be performed.

If lung re-expansion is unsatisfactory with evidence of trapped lung on chest X-ray (<50% pleural apposition on chest X-ray), then pleurodesis will not be attempted and the drain removed with early follow-up of the patient to consider repeated drainage of the effusion or IPC insertion if symptomatic.

If pleurodesis is performed, it will be carried out as per the BTS guidelines. Then, 3 mg/kg (maximum 250 mg) of 1% lignocaine will be administered via the chest drain. This will be followed by 4 g talc mixed with 50 mL saline instilled through the drain, followed by 50 mL saline flush of the drain into the pleural cavity. The drain will be clamped and left closed for 1 hour. After this time, the drain will be opened and left on free drainage for 24–72 hours. If the fluid output is <250 mL per day, the drain will be removed and patient will be discharged home. Complications, drain output and the use of thoracic suction (which will be at the discretion of the treating team) will be recorded. If the output is high, the drain will be left longer and depending on the clinical assessment as per the standard practice, the drain will be removed.

Patients will have follow-up on the 7th day and 14th day postprocedure. During each follow-up, they will undergo a chest X-ray and chest ultrasound and be asked to complete the QoL and symptom questionnaires. They will also undergo the same assessment at follow-up 30, 60 and 90 days after the intervention. If the pleurodesis is not successful, they will have further assessment and will be managed based on clinical requirement regarding the need for further pleural intervention.

Patients may choose to withdraw themselves from the trial. If a patient does so, we will retain the data the patient has previously consented for us to collect and analyse. No further data would be collected. It will be made very clear to the patient throughout their follow-up that a decision to withdraw from the trial will not prejudice any future medical care they receive. On completion of the trial, patients will receive normal medical care as per local practices.

### Sample size calculation and statistical analysis

In this ANCOVA study, sample sizes of 71 and 71 are needed from each of the 2 groups whose means are to be compared. The covariate has an *R*^2^ of 0.49 (0.7 correlation between baseline and follow-up). A total sample of 142 participants achieves 80% power to detect a clinically significant difference of 8 points in global health status at 30 days among the means versus the alternative of equal means using an F test with a 5% significance level. The minimally important difference in global health status is based on reference values provided by the EORTC Quality of Life Group.^15^ The common SD within a group is assumed to be 23.60, derived from EORTC reference values (all patients with cancer: stages III and IV).^15^ Therefore, the randomisation target is 142 participants. The interim analysis is planned when 50% of the randomisation target has been reached and will include review of recruitment, follow-up rates and the randomisation target.

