### Recruitment and randomisation

Enrolment started in July 2015 and is anticipated to continue until January 2020. In each centre, the trial team will screen patients presenting to the respiratory and oncology clinics as well as inpatient wards.

Once screening procedures have confirmed a patient's eligibility, they will be approached and consented for the study. They will undergo stratified randomisation (1:1) to either usual care as per BTS guidance or treatment with an IPC. This will be performed using a web-based secure randomisation service for clinical trials (http://www.sealedenvelope.com). The stratification variables are age (<65 years, ≥65 years), malignancy subtype (lung, mesothelioma, breast, other) and WHO performance status (0, 1, 2, 3). Given the nature of the intervention, patients and the research team will not be blinded.

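### The article names an ANCOVA with baseline score as its only covariate although randomisation is stratified on three factors; the primary model should include those factors as main effects

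*Protocol article*

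**What the plan says.** Under Recruitment and randomisation, the article says "They will undergo stratified randomisation (1:1) to either usual care as per BTS guidance or treatment with an IPC". It then lists the factors: "The stratification variables are age (<65 years, ≥65 years), malignancy subtype (lung, mesothelioma, breast, other) and WHO performance status (0, 1, 2, 3".

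Under Sample size calculation and statistical analysis, it describes the design as an ANCOVA: "In this ANCOVA study, sample sizes of 71 and 71 are needed from each of the 2 groups whose means are to be compared". Its covariate is in the singular, with an R² of 0.49 explained as "0.7 correlation between baseline and follow-up". The other inputs are "A total sample of 142 participants achieves 80% power to detect a clinically significant difference of 8 points in global health status at 30 days", "using an F test with a 5% significance level" and "The common SD within a group is assumed to be 23.60". The section closes with "Therefore, the randomisation target is 142 participants".

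This is the article's only text on how the arms are to be compared. It mentions no stratification factor. It also does not list the terms of the final primary model, and it does not say that the factors are excluded.

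**The concern.** Stratifying on a prognostic factor balances it between the arms and so lowers the true sampling variance of the treatment difference. An analysis that leaves the factor out keeps its variance in the residual term, so the reported standard error does not reflect the reduction. Confidence intervals are then wider than they need be, and the test rejects less often than its nominal 5% when there is no effect.

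The ANCOVA that the article names does not match the randomisation that it describes. If that model were carried into the primary analysis unchanged, the trial would give up precision that its stratification had already secured. Precision is at stake here, not bias or false-positive risk.

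**Working it through.** **Inputs from the article.** Difference 8 points, within-group SD 23.60, baseline R² 0.49, two-sided 5% (an F test with two groups), 71 per arm. Strata: 2 × 4 × 4 = 32 cells, about 142/32 = 4.4 patients each. As main effects the factors use 1 + 3 + 3 = 7 degrees of freedom.

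**Reproducing the plan's figure.**
- Residual SD = 23.60 × √(1 − 0.49) = 16.85.
- SE of the difference = 16.85 × √(2/71) = 2.83.
- The noncentral F test with 2n − 3 error degrees of freedom gives 79.6% power at 70 per arm and 80.2% at 71.

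The stated 71 per arm is therefore exact for an ANCOVA with baseline alone.

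**Input not in the article.** Let e be the share of residual variance, after baseline, that the three factors explain. It is assumed here over the range 0 to 0.20.

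**Formulas, taking the strata as balanced.**
- Reported SE, baseline-only model: 2.83 at every e.
- True SE: 2.83 × √(1 − e).
- Overstatement of the SE: 1/√(1 − e) − 1.
- True type I error, baseline-only: 2 × [1 − Φ(1.977/√(1 − e))], where 1.977 is the t critical value on 139 df.
- Power, baseline-only: 1 − Φ((1.977 × 2.83 − 8)/true SE).
- Power, adjusted: noncentral F with residual SD 16.85 × √(1 − e) and 142 − 3 − 7 = 132 df.
- 95% CI half-width, baseline-only: 1.977 × 2.83 = 5.59 points. Adjusted: 1.978 × true SE.

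| e | SE too large by | Type I error, baseline-only | Power, baseline-only | Power, adjusted | CI half-width, adjusted |
|---|---|---|---|---|---|
| 0 | 0% | 4.8% | 80.3% | 80.2% | 5.60 |
| 0.02 | 1.0% | 4.6% | 80.5% | 81.0% | 5.54 |
| 0.05 | 2.6% | 4.3% | 80.9% | 82.1% | 5.45 |
| 0.10 | 5.4% | 3.7% | 81.5% | 84.1% | 5.31 |
| 0.20 | 11.8% | 2.7% | 82.9% | 88.1% | 5.00 |

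The 4.8% in the first row comes from the normal approximation; with e = 0 the test has its nominal 5%. In that row adjustment costs about 0.1 points of power.

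**Check without perfect balance.** With 4.4 patients per cell many blocks stay incomplete, so the case was also simulated. Blocks of 4 and the factor prevalences were assumed, since the article gives neither.
- e = 0.10: type I error 4.2% baseline-only against 5.1% adjusted; power 80% against 82%.
- e = 0.20: type I error 3.6% against 5.0%; power 81% against 87%.
- e from 0 to 0.05: almost no difference.

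**The case against.** The strongest reply is that the single covariate is an input to a power calculation, not a specification of the fitted model. Sizing on baseline alone is a normal and conservative choice, and it does not commit the analysis to omitting anything. The final covariate list is commonly left to a statistical analysis plan, which is not shown, and a journal article condenses the full protocol. This stands. A reader might infer that the trial will leave the strata out of its analysis; the article does not establish that.

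Second, the size of any loss is assumed. The baseline score already accounts for 49% of the variance, and the factors may add little to it. At e = 0.02 the forgone gain is 0.5 points of power, and at e = 0 it is nil. This also stands, so too-wide intervals cannot be asserted as certain.

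Third, the mechanism partly limits itself. The overstated standard error depends on balance, and 32 small cells leave balance incomplete. The simulated type I error of 3.6% at e = 0.20, against 2.7% by formula, shows this. However, incomplete balance also leaves chance differences that only adjustment corrects, and the simulated power gain at e = 0.20 is no smaller than the one by formula.

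What remains is that the one analysis named does not match the randomisation described, and that aligning them costs almost nothing.

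**Conclusion.** The point holds as a minor one, conditional on the primary analysis following the named model. Over an assumed e of 0 to 0.20, the standard error is 0 to about 12% too large (the upper figure assumes balanced strata). Type I error falls from 5% to roughly 3%, and about 0 to 6 percentage points of power are forgone. Below e = 0.05 the effect is negligible.

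Two stronger readings are tempting and not supported. One is that the trial becomes underpowered: baseline-only power stays at about 80% or above with all 142 analysed, so the loss is a forgone gain and not a shortfall. The other is that the omission makes the test invalid: the error is in the conservative direction. The figure of 142 is correct for the model it was computed from.

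**What to change.** State, or confirm if an analysis plan already says so, that the primary analysis is an ANCOVA of day-30 global health status on arm, baseline score, age group, malignancy subtype and WHO performance status. Enter the three factors as main effects and not as 32 cells. If sparse levels are to be merged, write the rule down before any comparative data are seen, so that it cannot depend on the result.

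The cost is one sentence and 7 model degrees of freedom, about 0.1 points of power if the factors explain nothing. All three variables are needed at randomisation, so no new data are collected. The sample size stays at 142. Nothing in this check calls for a centre term.

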**Methods and analysis:**

OPTIMUM is a multicentre non-blinded randomised controlled trial. Patients with a diagnosis of MPE will be identified and screened for eligibility. Consenting participants will be randomised 1:1 either to an outpatient ambulatory pathway using IPCs and talc pleurodesis or standard inpatient treatment with chest drain and talc pleurodesis as per British Thoracic Society guidelines. The primary outcome measure is global health-related QoL at 30 days measured using the EORTC QLQ-C30 questionnaire. Secondary outcome measures include breathlessness and pain measured using a 100 mm Visual Analogue Scale and health-related QoL at 60 and 90 days. A sample size of 142 patients is needed to demonstrate a clinically significant difference of 8 points in global health status at 30 days, for an 80% power and a 5% significance level.

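### The 142 patients needed in the analysis for 80% power are also the number to be randomised, with no allowance for missing day-30 scores and no stated rule for raising the target at the interim review

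*Protocol article*

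**What the plan says.** The section on sample size calculation and statistical analysis sets out an ANCOVA comparison of two means, with 71 patients needed per group. The inputs are all given: "a clinically significant difference of 8 points in global health status at 30 days", "The common SD within a group is assumed to be 23.60", a baseline-to-follow-up correlation of 0.7 (R-squared 0.49), and a test "using an F test with a 5% significance level". The power statement is "A total sample of 142 participants achieves 80% power to detect a clinically significant difference of 8 points", and the section then draws its conclusion: "Therefore, the randomisation target is 142 participants".

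The same number appears elsewhere. The abstract says "A sample size of 142 patients is needed to demonstrate a clinically significant difference of 8 points". The study population section gives 142 as the number to be recruited, and the discussion calls it the recruitment target.

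The article also foresees losses:
- The introduction describes the population's prognosis as poor.
- The list of expected adverse events includes death from the underlying cancer.
- At the end of the usual care section: "Patients may choose to withdraw themselves from the trial". Data already collected are then kept, but nothing more is collected.

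An interim analysis is planned at 50% of the randomisation target. It covers recruitment, follow-up rates and the target. The data management section assigns it to the trial statistician, independently of the investigators.

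**The concern.** A sample size for comparing means counts patients whose outcome is in the analysis. A randomisation target counts patients who enter the trial. The two are equal only if nobody lacks the outcome. Here the outcome is a self-completed questionnaire at day 30, which a patient who has died cannot give and a patient who has withdrawn will not be asked for.

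The article moves from the first number to the second in one step, while listing death and withdrawal as things that will happen. The 80% in the abstract and in the sample size section therefore describes a trial with complete day-30 data. The 8 points are presented as the minimally important difference, so any shortfall is in power for the very effect the trial was sized to find.

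**Working it through.** **Inputs**, all from the section on sample size calculation and statistical analysis: difference 8; within-group SD 23.60; R-squared 0.49; F test at 5%, which for two groups is a two-sided test; equal groups. The article gives no loss rate, so the loss rates below are assumptions.

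**Step 1: reproduce the stated figure.**

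Residual SD = 23.60 × √(1 − 0.49) = 23.60 × √0.51 = 16.85.

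With N patients analysed, half in each arm and one covariate, the F test has 1 and N − 3 degrees of freedom and noncentrality λ = (N/4) × (8/16.85)².

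For N = 142: (8/16.85)² = 64/284.05 = 0.2253, and λ = 35.5 × 0.2253 = 8.00. The 5% critical value of F on 1 and 139 df is 3.91. Power = 80.2%.

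The smallest group size that reaches 80% is 71, so the stated figure is reproduced exactly. Other readings of the inputs do not give 71 (normal approximation in each case): ignoring the covariate needs 137 per group, a one-sided test 55, and a change score 82. The normal approximation for the ANCOVA itself gives 70 per group.

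**Step 2: look for hidden reserve.**

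| Patients analysed | Power |
|---|---|
| 142 | 80.2% |
| 141 | 79.9% |
| 140 | 79.6% |
| 138 | 79.1% |

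Rounding up has not left an allowance for loss inside the 142.

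**Step 3: apply loss to 142 randomised.** The number analysed is 142 × (1 − d), where d is the proportion without a day-30 score. Such patients are taken to contribute nothing (complete-case basis), and loss is taken to be equal in the two arms.

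| Assumed loss d | Analysed | λ | Power |
|---|---|---|---|
| 0% | 142 | 8.00 | 80.2% |
| 5% | 134.9 | 7.60 | 78.1% |
| 10% | 127.8 | 7.20 | 75.9% |
| 20% | 113.6 | 6.40 | 70.8% |
| 30% | 99.4 | 5.60 | 64.9% |

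**Step 4: what keeping 80% would take, for scale.** Randomised per arm = 71/(1 − d), rounded up:
- 5%: 71/0.95 = 74.7, so 75 per arm, 150 in all.
- 10%: 71/0.90 = 78.9, so 79 per arm, 158 in all.
- 20%: 71/0.80 = 88.75, so 89 per arm, 178 in all.
- 30%: 71/0.70 = 101.4, so 102 per arm, 204 in all.

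**The case against.** **The interim review is aimed at this risk.** At half the target, the trial statistician will look at follow-up rates and at the target itself, so 142 is open to revision. This stands as mitigation. A reader might infer that the trial must end below its stated power; the article does not support that, because the target could be raised. But the review has no expected loss to compare against and no rule for acting on what it finds, and the 80% is stated without qualification.

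**The size of the loss is unknown.** This stands. Day 30 is the earliest of the three main assessments, and entry is limited by performance status. The article shows that losses are foreseen, not how many, and nothing in it points to 20% or 30% in particular. The printed survival criterion, under three months, may be a misprint and is not relied on here.

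**A single loss is trivial.** This stands too. A reader might infer that any one death breaks the power claim. It does not: 141 analysed gives 79.9% and 140 gives 79.6%, and both round to the stated 80%.

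**Partial data may help.** The questionnaire is also completed at baseline, day 7 and day 14, and data collected before withdrawal are kept. An analysis plan, not shown here, could use those scores, so the complete-case figures may be somewhat pessimistic. Earlier scores will not exist for everyone, and death by day 30 raises a separate question. In general, handling of missing data cannot make 142 randomised patients worth 142 observed day-30 scores.

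**Other inferences.** A reader might conclude that the sample size was miscalculated. It was not: 71 per group is correct for the stated inputs. A reader might also note that the 0.7 correlation carries no source and treat it as part of this problem. That is a separate matter, an article often leaves such sourcing to the full protocol, and the point here holds with 0.7 accepted.

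**Conclusion.** The point holds in limited form. The stated inputs need 71 analysed patients per arm, and the article sets the number randomised at the same 142 with no allowance for missing day-30 scores, despite foreseeing deaths and withdrawals. The 80% is therefore a complete-follow-up figure presented as the power of the trial as recruited.

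The shortfall depends on a loss rate that the article does not give. It is about 2 percentage points at 5% loss, about 4 at 10%, 9 at 20% and 15 at 30%. That is minor at 5% and material from about 10%. These figures assume the stated SD and correlation, equal loss in the two arms, no information from patients without a day-30 score, and no change of target at the interim review. The review reduces the risk but, as described, does not remove it.

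**What to change.** In the abstract and in the sample size section, say that 80% power applies to 142 patients with a day-30 score. State the day-30 loss the sponsor expects, which only the sponsor can supply, and give the resulting power for 142 randomised: for example, about 76% at 10% loss or about 71% at 20%.

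Add one sentence to define the interim review already planned: it re-estimates day-30 completeness, the SD and the baseline-to-day-30 correlation from both arms pooled, with no comparison by arm.

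The cost is a less favourable stated power and that added sentence. The restatement itself needs no extra patients. If the sponsor prefers to keep 80%, the target has to rise to 142/(1 − d), as in the last step of the working, and the cost is then the added recruitment.

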### Trial management

The respiratory research team at St Thomas' hospital will oversee site initiation and training, screening log and data submission, data quality assurance and study close out. The sponsor Guy's and St Thomas' Hospital R&D development will oversee contracts agreements at each site. Sites will undergo regular monitoring by the coordinating trial team (consisting of the chief investigator, trial manager and trial coordinator) through both site visits as well as the assessment of submitted data quality and adverse events (AEs). A yearly progress report will also be submitted to the Health Research Authority.

### Data management

These data will be collected by the trial coordinator, principal investigators and research nurse. Patient data will be anonymised with trial number allocations. Data will be recorded on paper case report forms in booklets comprised of triplicate carbon copy paper. The data will be analysed by the clinical research fellow, the chief investigator and the trial statistician. This will primarily be performed at St Thomas' Hospital. This is an 18-month trial (total 3 months of follow-up) with subsequent data analysis and manuscript production. The VAS Score will be measured by two members of the trial team at the coordinating centre. Case Report Forms will be stored in locked filing cabinets. The completed case reports forms will undergo quality control assessment once the patient has completed or withdrawn from the trial by the trial coordinator and manager before transcription onto a password-protected database on a secure computer network. This will performed by two members of the trial team to ensure quality control and data reliability. As this is a non-CTIMP trial, a data monitoring committee is not required; however, the interim analysis will be performed by the trial statistician independent of the investigators.

### Adverse event reporting

Any serious adverse event (SAE) related to the study procedures or is an unexpected occurrence (ie, the type of event is not listed in the protocol as an expected occurrence) must be reported immediately on knowledge of the event to the sponsor within 24 hours. All other AEs must be reported to the sponsor when copied into the annual progress report. Given this is a multisite trial, the principal investigators at all sites must report all SAEs to the chief investigator first where possible. The chief investigator is responsible for reporting events to the sponsor.

#### Expected AEs

These events are expected based on what is already documented for events associated with the trial interventions. The following are considered to be expected AEs associated with the proposed interventions for this trial:

Chest drain and IPC insertion:
Pain at drain siteLocalised bleeding at drain siteLocalised infection at the drain siteEmpyemaPneumothorax

Talc pleurodesis
PainFever

Other expected AEs
Death secondary to underlying malignancyHospitalisation due to underlying malignancy or comorbid condition

These are well-acknowledged risks, and patients will be consented appropriately. Participant safety will be ensured through regular review and follow-up. During the procedures, vital signs including blood pressure and oxygen saturation measurements will be used to ensure patient well-being. Chest X-ray will be used to verify tube position.

